### Control and Intervention Groups

#### Control

Clients will receive usual publicly funded home care services provided by their provincial or regional home care agency including but not limited to home visits by assistive personnel for activities of daily living, nursing care, and other supports deemed necessary by the home care case coordinator or case manager. In both study sites, home care assessments are conducted by the regional authority case coordinator or case manager. Once the assessment is completed and care services are decided, service delivery is provided by a contracted home care agency.

#### Intervention

Clients will receive RMHC in addition to usual home care services. The intervention group will receive passive RM sensors to detect a combination of the following behaviors/movement patterns: medication administration, opening refrigerator/cupboards, getting in and out of bed, movement in the bathroom, use of exit doors, movement detection, and for observation (cameras). The study technology partner, CareLink Advantage (www.carelinkadvantage.ca), will cover the equipment and monitoring costs. Once enrolled in the study, clients and their family/friend caregivers will have a home visit by the technology partner (or designate). They will receive written and verbal overview of the various RM options. Based on the assessment by the technology partner along with client and family/friend caregiver preferences, the RM options will be customized and implemented. The intervention will be offered to the client for 12 months at which time the client will be transitioned to usual care. Notifications of atypical events (eg, missed medication, atypical length of time in bed) will be sent to the family/friend caregiver via either email, text message, or phone call. Action, based on the notification, may include a telephone call to prompt the client or check on the client’s safety, deployment of assistive home care supports, or emergency action (eg, ambulance). During the study, researchers will not receive any notifications. However, at the end of the study notification patterns and trends will be analyzed.

### Data Collection

Prior to initiating the PRCT, all research team staff in Nova Scotia and Ontario and study site care coordinators/case managers will receive training on the study protocol and data collection measures. In addition, research staff and home care agency staff will be educated about the RM equipment by the industry partner (CareLink Advantage).

#### Phase I: Survey Data Collection

Researchers will meet with clients and family/friend caregivers in the home of the client or by phone at baseline, 6 months, and 12 months to collect data. It is expected the interviews will last no more than one hour. Paper format questionnaires including standardized instruments and researcher-developed questions will be used to collect data at each time point (see Measures). Data on reasons for leaving the study will also be collected. A demographic form will be used to collect basic demographics including age, education, sex, marital status, income, and individuals’ provincial health insurance number. The provincial health insurance number will be used for data linkage to provincial administrative health care databases in order to conduct the economic evaluation.

#### Phase II: Administrative Data Linkage

To address the primary outcome of the study, data will be obtained from the regional health authorities related to the occurrence of and time to events such as trips to emergency, short-term admission to hospital, terminal admission to hospital, and direct admission to long-term care.

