### Sample Size Calculation

The sample size calculation is based on data from one health region included in the study to estimate the study’s main outcome (time to higher levels of care). The following criteria were used to estimate sample size: the total institutionalization proportion among controls being equal to 0.41 and the proportion or the experimental subjects at 0.27 (ie, a 34% reduction compared to controls); a 10% dropout and/or lost to follow-up rate; a power of 80% and a statistical significance level of alpha=.05. This resulted in an estimate of 160 participants for the intervention group and 320 for the control group for a total target study size of 480 participants across the study sites [25,26]. We opted to increase the study power by using a 2:1 ratio of controls to intervention subjects due to the cost of the intervention.

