### Data Analysis

#### Quantitative Data

Quantitative data will be analyzed at baseline, with subsequent analysis of primary/secondary outcomes at 6 months and 12 months. Using SPSS Statistics version 25 (IBM Corp) statistical software, descriptive statistics will provide a profile of study participants including demographics, current diagnoses, length of home care before the study, and model of care (RMHC versus usual care). The provisional effect of the intervention on the primary outcome will be tested using a prospective chi-square test of independence (continuity-corrected) between the experimental and control groups (Fisher exact test). Repeated measures analysis of variance will measure mean differences between groups on continuous variables. We intend to use multivariate survival analyses methods using a relevant time dependent outcome based on the ability to accurately track the main event of interest (ie, institutionalization) [24]. We will conduct within and between province analyses on secondary outcomes. Subgroup analyses will include examining differences based on sex (male/female) in both clients and family/friend caregivers.

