## Results

The end of data collection for the primary outcome (occurrence of and time to terminal admission to hospital awaiting admission to long-term care and direct admission to long-term care) will be winter 2020. Data collection for the secondary outcome (health service use) will continue for up to 5 years after the 12-month participant interview. Qualitative data will be collected during study years 3 through 5.

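### Emergency trips and short hospital stays can recur but are described by the same occurrence and time-to-event metric as institutionalization, and no rate comparison is named for them

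*Protocol article*

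**What the plan says.** The Abstract (Objective) and Phase II: Administrative Data Linkage list four kinds of event under the primary outcome. Phase II says that data will be obtained on the "occurrence of and time to events such as trips to emergency, short-term admission to hospital", followed by terminal hospital admission and direct long-term care admission. Study Design, Measures and Results give a narrower primary outcome: terminal hospital admission and direct long-term care admission only.

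Quantitative Data assigns the primary outcome a "prospective chi-square test of independence (continuity-corrected) between the experimental and control groups", with Fisher's exact test in brackets and the effect called provisional. Survival methods are intended, with institutionalization as the main event. Repeated-measures analysis of variance is for continuous variables. No count, rate or recurrent-event method is named.

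Health Care Costs takes hospitalizations and emergency room visits from administrative databases. Economic Analysis multiplies each client's resource use by unit costs and regresses the total on arm. Results treats service use as secondary: "Data collection for the secondary outcome (health service use) will continue" for up to five years after the 12-month interview.

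**The concern.** Occurrence and time to event suit an event that can happen once. Clients with complex needs may go to emergency several times in a year. An any-event analysis scores one trip and six trips alike, and a first-event analysis ignores everything after the first trip. Remote monitoring is meant to let a caregiver step in early, so fewer trips per client is at least as plausible an effect as more clients with no trip at all. The metric given for these events sees the first kind of effect poorly.

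The cost regression does use repeat events, but its outcome is a money total that combines emergency visits, hospital stays, home care and the intervention's own fees. It cannot say whether emergency trips or short admissions fell.

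The two definitions of the primary outcome add to the problem. Under the Abstract and Phase II, the chi-square test would reach a set of events that includes emergency trips. Under Study Design, Measures and Results it would not, and these events would have no named effect analysis apart from cost.

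**Working it through.** **1. The plan's own figure.** Sample Size Calculation gives "the total institutionalization proportion among controls being equal to 0.41", "the experimental subjects at 0.27 (ie, a 34% reduction compared to controls", "a power of 80% and a statistical significance level of alpha=.05", "a 10% dropout and/or lost to follow-up rate" and "using a 2:1 ratio of controls to intervention subjects".

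- Weighted mean proportion: (0.27 + 2 × 0.41)/3 = 0.3633.
- Uncorrected, two-sided: n = [1.96√(1.5 × 0.3633 × 0.6367) + 0.8416√(0.27 × 0.73 + 0.41 × 0.59/2)]² / 0.14² = (1.1545 + 0.4746)²/0.0196 = 135.4, so 136 intervention clients.
- With continuity correction: 145.9, so 146.
- With 10% dropout: 146/0.9 = 162.2, so 163 (total 489); or 146 × 1.1 = 160.6, so 161 (total 483).

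The stated 160 + 320 = 480 is therefore reproduced closely. It concerns institutionalization and says nothing about power for emergency trips.

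**2. Power for the recurrent events.** Clients after 10% dropout: 160 × 0.9 = 144 and 320 × 0.9 = 288. Follow-up is 12 months. The article gives no event rate, dispersion or effect for these events, so all three are assumed: control rate μ of 0.5 to 3 per year, negative binomial dispersion k of 0 to 3, and rate ratio 0.66 (close to the relative reduction used for institutionalization) or 0.75.

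- Any event: P = 1 − (1 + kμ)^(−1/k), or 1 − e^(−μ) when k = 0; then a two-sided comparison of proportions, without continuity correction.
- First event: simulated log-rank test, 2,000 runs per setting.
- Count: SE of the log rate ratio = √[(1/μ₁ + k)/144 + (1/μ₀ + k)/288]; power = Φ(|ln RR|/SE − 1.96).

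Worked example, μ₀ = 1, k = 1, RR = 0.66:

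- Any event: 1 − 1/2 = 0.500 against 1 − 1/1.66 = 0.398. The standard error is 0.0509 under no difference and 0.0503 under the alternative. Power = Φ[(0.1024 − 1.96 × 0.0509)/0.0503] = 0.52.
- Count: SE = √(2.515/144 + 2/288) = 0.156. Power = Φ(0.4155/0.156 − 1.96) = 0.76.
- Power kept by the any-event analysis: 0.52/0.76, about 69%.

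Selected settings at RR 0.66:

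| Control rate per year | Dispersion | Any event | First event | Count |
|---|---|---|---|---|
| 0.5 | 0.5 | 0.52 | 0.52 | 0.63 |
| 1 | 1 | 0.52 | 0.53 | 0.76 |
| 2 | 0 | 0.90 | 0.96 | >0.99 |
| 2 | 2 | 0.33 | 0.40 | 0.70 |
| 3 | 3 | 0.22 | 0.24 | 0.59 |

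Over the whole grid, including RR 0.75, the any-event analysis keeps 37% to 91% of the count analysis's power and the first-event analysis keeps 41% to 98%. The loss thus runs from about 2% to about 63%, and the count analysis was ahead in every setting.

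A separate simulation at an assumed rate ratio of 0.7 agreed in direction: power 0.24 to 0.38 for any event (corrected chi-square) and 0.52 to 0.82 for the rate test. The rate test's type I error was near 5%.

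**3. Which time at risk.** Days living at home depend on the primary outcome. Assume no effect on trips, 1.5 trips per year in both arms, institutionalization 0.27 against 0.41, and a gamma frailty shared by trips and institutionalization. Trips per day at home then give a rate ratio of about 1.05, 1.1 and 1.24 at frailty variance 0.5, 1 and 2: a spurious excess in the intervention arm, because frailer clients stay longer in its denominator. Counting all trips over the full 12 months gives 1.5/1.5 = 1.00 by construction.

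**The case against.** The strongest reply has four parts.

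- **Repeat events are not thrown away.** They are captured, costed per client and compared between arms, and service use is a named secondary outcome. This stands: a reader might infer that the plan discards them, and the Health Care Costs, Economic Analysis and Results sections show otherwise. What remains is that a cost total yields no effect estimate for trips or short stays.
- **Phase II is about obtaining data.** It does not restrict these events to the first one, and the yes/no coding in Measures covers only the two terminal events. This stands in part. No yes/no coding is stated for emergency trips, and the chi-square test reaches them only if the Abstract and Phase II define the primary outcome. Still, occurrence and time to event is the only metric given for these events outside the cost analysis.
- **A condensed article may leave the model to the analysis plan.** The absence of a count model alone would not be a finding. The point rests on what is written: one metric for two kinds of event, and two conflicting accounts of which events are primary.
- **A rate model can itself bias the result if time at home is the offset.** This is correct, as step 3 of the working shows, and it determines the offset used in the fix.

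**Conclusion.** The point holds as a worthwhile improvement. The metric stated for emergency trips and short admissions suits them less well than a rate, and the sections disagree on whether these events are primary.

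The direction of the power loss is consistent; its size is not known. The range of about 2% to 63% rests on assumed rates, dispersion and effects. It also assumes a constant proportional effect on all events, full one-year follow-up of 144 and 288 clients, and no competing death or institutionalization. A reader might infer that about half the power is lost. That happens only with frequent events, strong clustering or a smaller effect, and the documents do not show that any of these applies here.

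A reader might also infer that the trial is underpowered for its main question. It is not, on this ground: the sample size concerns institutionalization, reproduces closely, and is untouched by how emergency trips are counted.

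**What to change.** 1. Reconcile the Abstract and Phase II with Study Design, Measures and Results, so that the primary outcome is institutionalization only (terminal hospital admission or direct long-term care admission). Keep occurrence and time-to-event analysis for it.
2. Name emergency trips and short-term hospital admissions as secondary service-use outcomes. Analyse each as a number of events per client by a negative binomial (or robust Poisson) rate ratio, adjusted for province.
3. Count all events from randomization to 12 months wherever the client lives, with the log of days alive and under observation as offset. Use days at home only in a sensitivity analysis, because it depends on the primary outcome.
4. Report deaths by arm beside the rate ratios, since death remains a competing event.

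The cost is wording and a little extra analysis. Time-to-event data already need event dates, and the costing already needs each client's volume of use, so no new participants or visits are required.

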#### Phase III: Qualitative Interviews and Focus Groups

Qualitative data will be collected in the form of semistructured interviews to understand the perspectives of clients, family/friend caregivers, health care professionals, and health care decision-makers on the use of RM in the home. Eight to 12 individuals each of clients, family/friend caregivers, health care professionals, and health care decision-makers will be interviewed. Interviews will be audio recorded and transcribed verbatim. To ensure accuracy of the transcribed data, a random selection of transcripts will be validated with audio recording. Interviews will focus on understanding views on the technology itself including acceptability/resistance (eg, privacy), the model of care (eg, client-centered), enhancements/improvements, and benefits of the model for clients, family/friend caregivers, health care professionals, and health care decision-makers. These data will assist with understanding implementation and evaluation of the model, inform modifications to the model for potential scale-up, and integrate end user perspectives into model refinements.

### Measures

The primary outcome of the study is the occurrence of and time to leaving one’s home for a higher level of care such as long-term care. This will be assessed using the following variables available in the Discharge Abstract Database for Ontario and Nova Scotia: terminal admission to hospital (yes/no) and direct admission to long-term care (yes/no).

Secondary outcomes are described below along with their specific measures. All standardized instruments have been validated in previous studies. Different versions of researcher-developed instruments were developed for clients and family/friend caregivers.

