## Methods

### Study Design

This 4-year study is an unblinded pragmatic randomized controlled trial (PRCT) with two parallel arms [19-22]. PRCTs are well-suited to supporting decisions about complex interventions tested in the real world when comparing with usual care [23,24]. The objective of the study is to examine the effectiveness of the RMHC versus usual home care in maintaining the client in their place of residence and delaying or preventing admission to higher levels of care such as hospitalization or long-term care.

This study builds on the findings of previous pilot studies conducted in the provinces of New Brunswick, Alberta, Nova Scotia, and British Columbia. The primary aims of this study are to test whether (1) RM along with usual home care (the intervention) versus usual home care alone (control) allow older adults with complex care needs to remain in their home longer and delay or avoid admission to higher levels of care (eg, hospitalization and long-term care), (2) intervention is cost effective, and (3) intervention will improve the quality of life for clients and family/friend caregivers. The primary outcome for this study is the occurrence of and time to events such as terminal admission to hospital awaiting admission to long-term care and direct admission to long-term care. The secondary outcomes for this study are (1) health care costs, (2) client functional status and quality of life in the home, (3) family/friend caregiver stress, and (4) family/friend caregiver functional health status.

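### The protocol names two different sources for direct long-term care admission, and one of them is, by its name, a hospital-discharge file that may not cover entries made without a hospital stay

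*Protocol article*

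**What the plan says.** The Study Design section of the protocol article defines the primary outcome as the occurrence of, and time to, two events: "terminal admission to hospital awaiting admission to long-term care and direct admission to long-term care". The Abstract (Objective) and the Results section draw the same line between entry by way of hospital and direct entry.

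Three sections bear on where these events are found:

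- **Measures** names two yes/no variables, terminal hospital admission and direct LTC admission, and gives one source for both: "This will be assessed using the following variables available in the Discharge Abstract Database for Ontario and Nova Scotia".
- **Phase II: Administrative Data Linkage** names another source for the primary outcome: "data will be obtained from the regional health authorities related to the occurrence of and time to events". Its list of events is "trips to emergency, short-term admission to hospital, terminal admission to hospital, and direct admission to long-term care", so it includes direct LTC admission.
- **Phase I: Survey Data Collection** says the provincial health insurance number will be "used for data linkage to provincial administrative health care databases in order to conduct the economic evaluation". The primary outcome is not mentioned there.

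The Quantitative Data section makes the survival analysis depend on whether institutionalization can be tracked accurately.

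**The concern.** A direct admission, as the article uses the term, is the one that does not pass through the terminal hospital stay. A file of hospital discharges is a doubtful place to find it. Measures nevertheless assigns it there, while Phase II points to the regional authorities for the same event. A data analyst working from Measures and one working from Phase II could count different events.

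Two things are at stake. First, if direct admissions are not captured, those clients are scored as still at home, events are lost and power falls. Second, capture would depend on the route into LTC. Monitoring gives caregivers information that might change that route. If it does, the arms would be compared on which route clients took as well as on whether they left home, and a larger sample would not cure that.

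**Working it through.** **1. The sources side by side**

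| Section | Source named | Direct LTC admission included? | Timing |
|---|---|---|---|
| Measures | Discharge Abstract Database | Yes, as a yes/no variable | Outcome is time-to-event, but only yes/no variables are listed |
| Phase II | Regional health authorities | Yes, in the event list | Occurrence and time |
| Phase I | Provincial administrative databases, by health number | Not mentioned; stated purpose is the economic evaluation | – |

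No section says which source prevails, or whether the regional authorities are simply the route by which the database is obtained.

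**2. The plan's own sample size**

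Inputs from Sample Size Calculation: 0.41 (control), 0.27 (intervention), 80% power, alpha 0.05, 10% dropout, two controls per intervention participant. Two-sided testing is assumed because the sidedness is not stated. The Quantitative Data section specifies a continuity-corrected chi-square test.

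With r = 2, d = 0.41 − 0.27 = 0.14 and p̄ = (0.27 + 2 × 0.41)/3 = 0.363:

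- Uncorrected: n = [1.96·√(1.5·p̄(1−p̄)) + 0.842·√(0.27·0.73 + 0.41·0.59/2)]² / d² = (1.1545 + 0.4746)²/0.0196 = 135.4.
- Continuity-corrected: n' = (n/4)·[1 + √(1 + 2(r+1)/(n·r·d))]² = 33.85 × (1 + √1.158)² = 145.9, so 146 intervention and 292 control.
- Dropout: 146 × 1.10 gives 161 and a total of 483; 146/0.90 gives 163 and a total of 489.

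The stated 160 + 320 = 480 is within 3% of both. The sample size arithmetic is not in question.

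**3. Power if a share f of events is not captured, equal in both arms**

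Evaluable numbers: 160 × 0.9 = 144 and 320 × 0.9 = 288. Captured rates: 0.27(1−f) and 0.41(1−f).

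Power = Φ[(d − c − 1.96·se₀)/se₁], where se₀ uses the pooled rate and se₁ the two separate rates. Without correction c = 0; with continuity correction c = ½(1/144 + 1/288) = 0.0052.

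At f = 0: se₀ = 0.0491 and se₁ = 0.0470. The uncorrected argument is 0.93 (power 82%) and the corrected one 0.82 (power 79%).

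| f (assumed) | Captured rates, intervention / control | Power, uncorrected | Power, corrected |
|---|---|---|---|
| 0 | 0.270 / 0.410 | 82% | 79% |
| 10% | 0.243 / 0.369 | 76% | 72% |
| 25% | 0.2025 / 0.3075 | 64% | 60% |
| 50% | 0.135 / 0.205 | 42% | 37% |

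**4. Unequal routes**

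Captured rate = true rate × (1 − direct share). The splits are illustrative only.

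- No true effect (0.41 in both arms), direct share 40% in controls and 60% with monitoring: 0.41 × 0.6 = 0.246 against 0.41 × 0.4 = 0.164, an apparent 33% reduction.
- No true effect, milder split of 40% and 50%: 0.246 against 0.41 × 0.5 = 0.205, an apparent 17% reduction.
- The planned effect is real (0.41 against 0.27) and the split is reversed, 60% in controls and 40% with monitoring: 0.41 × 0.4 = 0.164 against 0.27 × 0.6 = 0.162. The benefit all but disappears.

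The bias can therefore go either way.

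**The case against.** The strongest reply is that nothing in the article shows an event being lost. Measures states that both variables are available in the database, and the article does not otherwise describe what the database holds. Phase II says the regional authorities will supply direct LTC admissions for the primary outcome. The trial team also contacts participants at 6 and 12 months and records reasons for leaving, which may reveal LTC entry. The article condenses a fuller protocol, where field-level sources would normally sit. Much of this stands, and it rules out several stronger readings that a reader might infer:

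- *That the database holds no record of home-to-LTC moves, so these events will be missed.* This is an inference from the database's name, and Measures asserts the contrary. Events are lost only if Measures is followed without Phase II and the file covers hospital stays only.
- *That Phase I restricts the health-number linkage to the economic evaluation.* It gives one purpose and excludes no other, and the next section, on administrative linkage, is expressly for the primary outcome.
- *That the trial would produce a spurious benefit close to the planned 34%.* The 33% comes from one chosen split; the reverse split hides a benefit. The resemblance is no evidence.
- *That event rates must fall below 0.41 and 0.27.* The planning data came from one health region, and the article does not say how events were ascertained there. If a similar file was used, the shortfall need not arise.

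The reply does not remove the conflict itself. The article states a source for the primary outcome in one section and a different one in another, and the source in Measures is doubtful for one of the two events. That is a conflicting statement, not detail left to a fuller document.

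**Conclusion.** The point holds as an unreconciled and potentially consequential statement of how a primary event is ascertained. It does not demonstrate that events will be lost. The harm requires that Measures alone is followed and that the Discharge Abstract Database covers hospital stays only; the documents settle neither. On those assumptions, and with equal loss in both arms, the illustrative fall in power ranges from a few percentage points (10% missed) to roughly half of the planned power (50% missed). The true share of direct admissions is not given, so no single figure can be stated. Unequal routes would add bias of unknown direction. Since the event is half of the primary definition and the correction is cheap, it should be settled before the outcome data are requested.

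**What to change.** - In Measures, take the occurrence and the date of direct LTC admission from the regional health authority data described in Phase II. Confirm for Ontario and for Nova Scotia that these data cover entries with no hospital stay. Phase II does not name a specific placement file, so the one used should be identified.
- Keep the Discharge Abstract Database as the source for the hospital route (terminal admission awaiting LTC), and make Phase II agree.
- In Phase I, state that the health-number linkage serves the primary outcome as well as the economic evaluation.

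The cost is wording, plus a check that the needed fields exist in each province and that the consent and data-sharing terms cover them. The sample size and the analysis do not change.
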